## Abstract

Background/Objectives: Innovative therapies are needed to reduce disability, facilitate activities of daily living, and improve the quality of life in patients with stroke. Non-invasive methods of stimulating the peripheral and central nervous system are increasingly being used to enhance the effects of existing therapies in stroke rehabilitation. One potentially relevant method for achieving greater improvement is repetitive peripheral magnetic stimulation (rPMS). This randomized controlled trial (RCT), the Peripheral MAgnetic stimulation in patients with spastic hemiparesis after Stroke Trial (REPMAST), will investigate whether rPMS improves upper extremity function, spasticity, and activities of daily living in patients with stroke compared with neuromuscular stimulation (NMS). Methods: REPMAST is an interventional, randomized controlled single-blinded study. Patients with subacute stroke are randomized to receive rPMS or NMS five days a week for three weeks in addition to standard rehabilitation therapy. The primary outcome is the change in the Fugl–Meyer Assessment for Upper Extremity between the beginning and end of the stimulation sessions. Secondary outcomes include changes in the Katz Index of Independence in Activities of Daily Living, the Timed Up and Go Test, the Modified Ashworth Scale, and the Tardieu Scale. A total sample size of 138 patients (69 in each group) is required to investigate the superiority of rPMS compared with NMS. Conclusions: The aim of this RCT is to provide evidence for an effective peripheral stimulation treatment for stroke recovery.

## 1. Introduction

Stroke is the third leading cause of death and disability combined worldwide [1]. Innovative therapies are needed to reduce disability, facilitate activities of daily living (ADL), and improve quality of life [2].

In recent years, in addition to physiotherapy and occupational therapy, non-invasive brain stimulation methods such as transcranial direct current stimulation and repetitive transcranial magnetic stimulation (rTMS) have been increasingly used to modulate brain function in order to improve functional deficits after stroke.

Another possibility to modulate brain function is through peripheral application, such as peripheral electrical stimulation [3,4] or with the use of repetitive peripheral magnetic stimulation (rPMS) [5,6]. Repetitive peripheral magnetic stimulation (rPMS) is a painless stimulation method that uses rapidly changing magnetic fields to stimulate peripheral nerves and trigger repeated contractions of the skeletal muscles. Using rPMS is simple compared with other NIBS approaches. The stimulation coil is placed directly on the skin in the area of the target muscle to be stimulated. The magnetic field penetrates the tissue and causes depolarization due to the electric field that builds up, resulting in the induction of an action potential, which clinically leads to muscle contraction. The rPMS method has also been used to stimulate peripheral nerves or spinal nerve roots, with the stimulation coil placed paravertebrally or over the corresponding nerve [7,8,9,10]. The exact mechanism of how rPMS interacts with the central and peripheral nervous systems is not yet fully understood. Struppler and colleagues suggested that rPMS causes increased proprioceptive input to the brain by activating mechanoreceptors of the contracted muscle [11]. Another type of input has been suggested to come directly from the nerve fibers. Consequently, rPMS increases sensory input from the affected limb to the brain, initiating neuroplastic processes and leading to improved sensorimotor performance in patients.

In the 1990s, the first studies by Struppler and colleagues reported improvements in perception, spasticity, and paresis after stroke and in patients with multiple sclerosis following the use of rPMS [12,13,14]. Over the past decade, the number of studies using rPMS has increased significantly [15]. Recent meta-analyses have reported that rPMS induces a better Fugl–Meyer Assessment for Upper Extremity (FMAUE) compared with control groups [16,17]. However, it has also been criticized that there is a lack of rPMS studies conducted as RCTs with large sample sizes [18,19,20]. Therefore, the current randomized controlled trial, the Repetitive Peripheral Magnetic stimulation in patients with spastic hemiparesis after Stroke Trial (REPMAST), will investigate the effect of rPMS compared to neuromuscular stimulation (NMS) in a large sample of patients with stroke. Because of the sensory influence of rPMS on the brain, the effect of rPMS in REPMAST will be compared with that of a control group that receives neuromuscular stimulation (NMS).

Previous reports have compared the advantages and disadvantages of rPMS and NMS [5,6,21]. It is important to note that although both interventions stimulate some common peripheral structures [6], they nevertheless activate different networks. Repetitive PMS has been found to increase activation of the ipsilesional superior posterior parietal and premotor cortex [11]. By contrast, NMS has been described to increase activity in the ipsilesional sensorimotor cortex [22]. Recent clinical studies have compared rPMS over muscles with sham [23], standard care [21], conventional physiotherapy [24], or its combination with low-frequency rTMS [10]. REPMAST is a randomized controlled comparative interventional trial that aims to investigate the efficacy (superiority) of rPMS compared with NMS in a large number of patients with subacute stroke, as there is no direct comparison between rPMS and NMS.

There are conflicting results regarding the effectiveness of rPMS in improving spasticity [14,16,18,19,20,23]. Therefore, this study will also analyze the effect of rPMS on spasticity.

## 2. Materials and Methods

### 2.1. Aim of the Study

The aim of the study is to compare the efficacy of rPMS and NMS in patients with an arm paresis in the subacute phase of stroke.

This research will be conducted in accordance with the Declaration of Helsinki and was approved by the local Ethics Committee on 22 August 2014 (No. 4147-07/14). The study is registered in the German Clinical Trials Register under the number DRKS00007899 (Universal Trail Number: 1111-1301-9734). Written informed consent to participate in the study will be obtained from each patient prior to the start of the study. A copy of the informed consent form will be given to each enrolled patient.

### 2.2. Patient Population and Eligibility Criteria

Participation in the study is voluntary. Each patient has the right to withdraw from the study at any time without giving a reason (withdrawal of consent) and without suffering any disadvantage. The patient will be asked to state the reason for withdrawal but will be advised that he/she is not required to do so.

The inclusion criteria are stroke onset within the previous six months (defined as ‘subacute stroke’) and a relevant arm paresis with at least one point within the subscore C of the FMAUE and an MAS score of ≥1.

The exclusion criteria for this study include a history of recurrent stroke, abnormal brain findings on CT or MRI images, pacemakers or other implanted devices, metals in the affected upper extremity, a history of epilepsy in the patient’s medical history, neurodegenerative disorders, psychiatric disorders, pregnancy, the use of antispastic medication, and botulinum toxin A injections in the affected upper extremity within the previous six months. Patients will also be excluded if they have a language comprehension disorder that makes it difficult for them to understand the rationale of the study. Patients will be recruited from an inpatient neurorehabilitation clinic. All admitted patients will be screened for eligibility for the study. All eligible patients will be informed about the contents of the REPMAST. They will be enrolled when they sign the written informed consent.

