### 2.3. Sample Size Calculation

REPMAST is designed to show the superiority of rPMS over NMS. Recently, the effect size of rPMS was calculated to be r = 0.68 for the FMAUE and r = 0.60 for the Wolf Motor Function Test when comparing rPMS with standard therapy [21]. A smaller effect size is expected here, as the comparison between rPMS and NMS contrasts two interventions. As there is still no RCT directly comparing rPMS and NMS, the final sample size was first compared by conducting a feasibility pilot study with 20 patients with stroke (10 in each intervention group) using the same inclusion and exclusion criteria as described above. According to the results of the feasibility pilot study, we found an effect size of 0.6 on FMAUE_Diff_ (the difference between Fugl–Meyer Assessment scores before and after the three-week stimulation session) for the rPMS group. Accordingly, to achieve a 90% statistical power to detect differences in FMAUE_Diff_ between the two groups at the 5% significance level (2-sided), a total sample size of 120 patients is required [25]. With an estimated drop-out rate of 15%, a total sample size of 138 patients (69 in each group) is required for this study.

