### 2.5. Randomization and Blinding

We will use a blocked randomisation procedure. Eligible patients will be blindly randomized into one of two groups, the rPMS group or the NMS group, using a randomization box with opaque sealed envelopes. An independent and impartial person will carry out the randomisation procedure (1:1 allocation ratio). The assessments are collected by neutral therapists who are not involved in the study. The person administering the stimulation is not involved in the motor testing. The therapists providing the rehabilitation therapy are also blinded to the patients’ affiliation. The data analyst is unaware of the patients’ allocation.

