### 2.7. Outcome Measures

The primary outcome is the difference between the Fugl–Meyer Assessment for Upper Extremity (FMAUE_Diff_) scores before and after the three-week stimulation session, calculated as follows: FMAUE_Diff_ = (FMAUE_post_ − FMAUE_pre_)/FMAUE_pre_.

The secondary outcomes are KADL, TUG, MAS, and TaS, which are calculated in the same way as the primary outcome of FMAUE_Diff_.

Correlation analyses will be used to analyze the relationship between arm spasticity (MAS and TaS), arm function (FMAUE), and independence in ADL (KADL) in each intervention group (rPMS and NMS). For this reason, a sum score will be calculated for a total MAS score (MAS_total_) of all the muscles assessed. The change in this score (between pre and post, MAS_total-Diff_) and TaS (TaS_Diff_) is correlated with the change in FMAUE (FMAUE_Diff_) as well as with the change in KADL (KADL_Diff_).

For each patient, stimulation and testing will be performed at the same time from Monday to Friday between 09:00 and 12:00.

During the trial, included patients may not be enrolled in other trials, treated with botulinum toxin or antispastic drugs, receive peripheral electrical stimulation, or receive peripheral or central magnetic stimulation (see Figure 2).

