### 2.8. Statistical Analysis

Statistical analysis will be based on the intention to treat analysis using IBM SPSS Statistics 29 (IBM, Armonk, NY, USA). The Kolmogorov–Smirnov Test will be used to test for normal distribution. Levene’s test will be used to assess the equality of variances between groups. If there is no normal distribution, the Mann–Whitney-U test will be used; otherwise, analysis of variance (ANOVA) will be used to test for differences in the repeated measures of FMAUE (pre, T1, T2, and post). In this 2 × 2 factorial design, group will be the independent factor and time will be the dependent factor. Post hoc analyses will be performed for significant main effects and interactions. One-way ANOVA will be used to ensure that the baseline FMAUE scores before the test are not statistically significant between the two groups. The same analysis will also be performed for KADL, TUG, MAS, and TaS.

For the within-group analysis (pre- and post-test), a paired *t*-test will be used if the distribution is normal; otherwise, the Wilcoxon test will be used.

For FMAUE_Diff_, two-sample *t*-tests will be used to test for the difference between the two groups (rPMS and NMS) if the distribution is normal. If the distribution is not normal, the Wilcoxon test will be used. The same analysis will be used for KADL_Diff_, TUG_Diff_, MAS_Diff_, and TaS_Diff_.

To analyze the relationship between arm spasticity (MAS) and arm function (FMAUE) and independence in ADL (KADL) in each intervention group (rPMS and NMS), correlation analyses between the MAS_total-Diff_ and (TaS_Diff_) and FMAUE_Diff_ as well as KADL_Diff_ will be used.

For missing follow-up measurements, the Last Observation Carried Forward (LOCF) procedure will be applied by inserting the most recent present value before.

The level of statistical significance will be set at *p* < 0.05, and Bonferroni correction will be used for multiple comparisons.

The effect size will be calculated using Cohen’s *d* according to the formula mean difference between two groups divided by the result of the pooled standard deviation (the pooled standard deviation is calculated as (=√[(standard deviation rPMS^2^ + standard deviation NMS^2^)/2])). The effect size will be defined as small (0.2), medium (0.5), or large (0.8) [40].

The primary safety endpoint is the incidence of seizures and headaches during the intervention period.

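### The primary comparison is fixed as unadjusted although time since stroke is known at entry; pre-specifying it as a covariate is a cheap improvement of uncertain size

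*Protocol article*

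**What the plan says.** **Eligibility (section 2.2).** "The inclusion criteria are stroke onset within the previous six months". Only an upper limit is given.

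**Outcome (section 2.7).** "The primary outcome is the difference between the Fugl–Meyer Assessment for Upper Extremity" before and after the three weeks of stimulation. The formula given divides this change by the pre-treatment score, so FMAUE_Diff is a relative change.

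**Analysis (section 2.8).** For FMAUE_Diff, two-sample t-tests "will be used to test for the difference between the two groups (rPMS and NMS) if the distribution is normal", with a Wilcoxon test otherwise. In the repeated-measures ANOVA of FMAUE, "group will be the independent factor and time will be the dependent factor". Neither analysis has a covariate. Baseline FMAUE, KADL, TUG, MAS and TaS are compared between arms; time since stroke is not on that list.

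**Randomisation (section 2.5).** "We will use a blocked randomisation procedure", with 1:1 allocation. No stratification factor is named.

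**Sample size (section 2.3).** From the pilot, "we found an effect size of 0.6 on FMAUE_Diff"; the 120 patients are meant "to achieve a 90% statistical power to detect differences in FMAUE_Diff_ between the two groups" at the two-sided 5% level, raised to 138 for 15% drop-out.

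**The concern.** The three-week treatment period can fall anywhere in a six-month window after stroke, and both arms also receive standard rehabilitation. Some of the variation in FMAUE change may therefore reflect how far along recovery a patient is and have nothing to do with the allocated stimulation. The eligibility check implies that the onset date is on file for every patient, so the value is available before randomisation without new data collection.

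An unadjusted test leaves any such variation in the error term. If the arms also happen to differ in time since onset, part of the observed group difference would come from that, and the planned test would not correct for it. At stake are some power and the accuracy of the estimate given the imbalance that actually occurs. The type I error rate is not affected.

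**Working it through.** **Inputs from section 2.3:** effect size d = 0.6 (outcome SD set to 1), two-sided alpha 0.05, target power 90%, 120 patients (60 per arm), 138 after allowance for drop-out (69 per arm).

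**Input not in the documents:** R², the share of the variance of FMAUE_Diff explained by time since onset. Assumed range 1–20%, with 0 as the worst case. In terms of the correlation rho, R² = rho².

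**Step 1: reproduce the plan's figure.** For an unadjusted two-sample t-test with n per arm, the noncentrality is d × √(n/2) with 2n − 2 degrees of freedom. At n = 60 this is 0.6 × √30 = 3.29, and the exact power is 90.3%. At n = 59 it is 89.8%. So 60 per arm, 120 in total, is the smallest size that reaches 90%. The plan's 120 reproduces, and it assumes no covariate.

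**Step 2: add the covariate.** Adjustment reduces the residual SD to √(1 − R²), so the effective standardised difference becomes d/√(1 − R²). At R² = 0.01 it is 0.6/√0.99 = 0.603. At R² = 0.20 it is 0.6/√0.80 = 0.671. The covariate uses one further degree of freedom (2n − 3), which does not change the figures below at one decimal.

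| R² (assumed) | Power, 60 per arm | Power, 69 per arm |
|---|---|---|
| unadjusted | 90.3% | 93.8% |
| 0 | 90.3% | 93.8% |
| 0.01 | 90.6% | 94.0% |
| 0.05 | 91.7% | 94.8% |
| 0.20 | 95.4% | 97.5% |

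The 69-per-arm column matters because section 2.8 specifies intention to treat with last observation carried forward, so up to all 138 patients may be analysed. The gain is 0.3 to 5.1 points with 60 per arm and 0.2 to 3.7 points with 69.

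**Step 3: chance imbalance.** With 60 per arm, the standardised difference in any baseline variable has SD √(2/60) = 0.183, so its 95% range is ±1.96 × 0.183 = ±0.36 SD. If onset times were uniform over 0 to 6 months (an assumption; SD = 6/√12 = 1.73 months), that is about ±0.62 months. An imbalance at that limit shifts the unadjusted contrast by rho × 0.36: about 0.04 SD at rho = 0.1 and 0.11 SD at rho = 0.3, against a design effect of 0.6.

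**The case against.** **The plan is not wrong.** The unadjusted test is valid under randomisation, and the sample size matches it exactly. Leaving out one prognostic factor is a choice about efficiency. This stands in full, and it sets the severity.

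**The gain is not shown.** No section reports any association between time since onset and FMAUE change. At rho = 0.1 to 0.2 (R² of 1–4%), power with 60 per arm rises only to 90.6–91.4%. This also stands, so the benefit can only be stated conditionally.

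**The spread may be narrower than six months.** The window is what entry permits. Patients are inpatients of a rehabilitation clinic with an MAS score of at least 1, and the actual range is not given. A narrower range would mean a smaller R².

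**Stronger inferences that the documents do not support.** A reader might infer that the planned comparison is biased. It is not: the usual type I error already allows for chance imbalance, and the shift in step 3 belongs to one particular realised allocation. A reader might infer that adjustment would balance the arms. It corrects for an imbalance; only the allocation procedure could create balance. A reader might also fault the randomisation as unstratified. The article names no factor, but a condensed article may leave that to the full protocol.

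What survives is narrow. The article does not leave the primary test open; it fixes one without a covariate. A plausible covariate is already held, and using it costs almost nothing even if it proves uninformative.

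**Conclusion.** The point holds as an inexpensive improvement of low severity. Section 2.8 fixes an unadjusted comparison while section 2.2 implies that time since stroke is known for everyone. Over the assumed 1–20% range the improvement in power runs from negligible to useful, and at R² = 0 there is essentially no loss.

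The conclusion rests on three assumptions: that the onset date is recorded for all patients (inferred from the eligibility rule), that the pilot effect size of 0.6 applies to FMAUE_Diff as the article states, and that R² lies in a range for which the documents give no evidence. The power figures refer to the relative-change outcome of section 2.7. They should not be carried over to an analysis of the post-treatment score, for which the article gives no effect size.

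**What to change.** In section 2.8, and in the analysis plan, make the primary between-group comparison a linear model for FMAUE_Diff with group and time since stroke onset as terms. Fix the covariate and its scale (for example, log days) before unblinding. Keep the planned unadjusted test as a sensitivity analysis.

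If the sponsor also prefers to analyse the post-treatment FMAUE score, baseline FMAUE should enter the model beside time since onset. That replaces the relative-change outcome of section 2.7, so it is a separate decision to be stated and justified as such.

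Cost: an amendment to the analysis wording and one degree of freedom. It needs no new patients and no new measurements, provided the onset date used for screening is kept in the trial data.

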### 2.3. Sample Size Calculation

REPMAST is designed to show the superiority of rPMS over NMS. Recently, the effect size of rPMS was calculated to be r = 0.68 for the FMAUE and r = 0.60 for the Wolf Motor Function Test when comparing rPMS with standard therapy [21]. A smaller effect size is expected here, as the comparison between rPMS and NMS contrasts two interventions. As there is still no RCT directly comparing rPMS and NMS, the final sample size was first compared by conducting a feasibility pilot study with 20 patients with stroke (10 in each intervention group) using the same inclusion and exclusion criteria as described above. According to the results of the feasibility pilot study, we found an effect size of 0.6 on FMAUE_Diff_ (the difference between Fugl–Meyer Assessment scores before and after the three-week stimulation session) for the rPMS group. Accordingly, to achieve a 90% statistical power to detect differences in FMAUE_Diff_ between the two groups at the 5% significance level (2-sided), a total sample size of 120 patients is required [25]. With an estimated drop-out rate of 15%, a total sample size of 138 patients (69 in each group) is required for this study.

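### The sample size section attributes the pilot effect size of 0.6 to the rPMS arm, yet 120 patients for 90% power follows only if 0.6 is the rPMS-versus-NMS Cohen's d

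*Protocol article*

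**What the plan says.** Section 2.3 of the protocol article sets the objective: "REPMAST is designed to show the superiority of rPMS over NMS". It cites effect sizes from an earlier comparison of rPMS with standard therapy (r = 0.68 for the FMAUE, r = 0.60 for the Wolf Motor Function Test) and adds: "A smaller effect size is expected here, as the comparison between rPMS and NMS contrasts two interventions". Because no trial has compared rPMS with NMS directly, a pilot with 10 patients per arm was run. Its result is given as an "effect size of 0.6 on FMAUE_Diff_ (the difference between Fugl–Meyer Assessment scores before and after the three-week stimulation session) for the rPMS group".

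The next sentence takes this as the basis for 120 patients "to achieve a 90% statistical power to detect differences in FMAUE_Diff_ between the two groups" at the two-sided 5% level. The total is then raised to 138 for 15% drop-out.

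Section 2.7 defines the primary outcome as "FMAUE_Diff_ = (FMAUE_post_ − FMAUE_pre_)/FMAUE_pre" (the denominator is the pre-treatment score). Section 2.8 plans a two-sample t-test on it if the data are normal. It defines the trial's effect size as Cohen's d: the difference between the group means over the pooled SD.

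**The concern.** The input is described as a property of one arm, while the conclusion concerns a contrast of two arms. Nothing printed connects them: section 2.3 gives no NMS change, no between-group difference and no SD.

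The distinction matters because the comparator is active. According to the abstract and section 2.6.2, NMS patients receive 15 stimulation sessions under the same two intensity criteria, in addition to standard rehabilitation, and they are within six months of stroke. Some gain under NMS is plausible. If 0.6 measures only how much rPMS patients changed, that gain has not been subtracted, and the 90% does not describe the superiority test. A non-significant result would then be read against a power figure that the trial may not have.

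**Working it through.** **Inputs.** Effect size 0.6, power 90%, two-sided alpha 0.05 and 120 evaluable patients (section 2.3); 1:1 allocation (section 2.5), so 60 per arm; two-sample t-test (section 2.8).

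**Reproducing the plan's figure, with 0.6 as the between-group d.**
- Normal approximation: n per arm = 2(1.960 + 1.2816)²/0.6² = 2 × 10.507/0.36 = 58.4, so 59 per arm and 118 in total.
- With the t distribution: 59.35, so 60 per arm and 120 in total. This is the stated figure.
- Power from the noncentral t with noncentrality d√(n/2): at 60 per arm, 0.6 × √30 = 3.286 on 118 degrees of freedom gives 90.3%. At 59 per arm it is 89.8%, so 120 is exactly the smallest balanced total that reaches 90%.

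**Other readings do not give 120.**
- 0.6 as a one-arm change tested against zero: n = 10.507/0.36 = 29.2, or about 30 patients.
- 0.6 as a correlation r, like the earlier figures in the section: d = 2 × 0.6/√(1 − 0.36) = 1.5, so n per arm = 2 × 10.507/2.25 = 9.3, or 20 in total.

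The calculation therefore used 0.6 as the rPMS-minus-NMS Cohen's d.

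**If 0.6 is the rPMS arm's own change.** Assumptions not in the document: equal SDs in both arms, 0.6 standardised by the SD of change, and an NMS change equal to a fraction f of the rPMS change. Then between-group d = 0.6 × (1 − f). With 60 per arm:

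| NMS share f | between-group d | power |
|---|---|---|
| 0 | 0.60 | 90.3% |
| 25% | 0.45 | 68.6% |
| 50% | 0.30 | 37.1% |

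Under these assumptions, 90% requires essentially no change under NMS: the smallest d with 90% power at 60 per arm is 0.597.

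**Power of 120 evaluable patients by between-group d, whatever its source.** 0.60: 90.3%; 0.50: 77.5%; 0.40: 58.4%; 0.30: 37.1%.

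**Precision of the pilot value (exact noncentral-t 95% intervals for 0.6).** As a between-group d with 10 per arm: −0.31 to 1.49. As a one-arm standardised change with n = 10: −0.09 to 1.26.

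**The case against.** The best defence is that the reference to the rPMS group is loose wording for a between-group d in favour of rPMS. Section 2.3 itself names the earlier effect against standard therapy after the experimental treatment alone. The pilot had two arms and was run because a direct comparison was lacking, section 2.8 defines effect size as between-group, and 120 reproduces exactly on that reading. This stands as a real possibility: the text cannot exclude it, and if it is right the 120 is correctly derived. It does not remove the point, because the printed sentence assigns the figure to one arm and gives nothing from which a reader could confirm the other reading.

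Three stronger readings are tempting, and the document does not support them.
- *The pilot effect was measured on the raw difference while the trial analyses a ratio.* Section 2.3 does gloss FMAUE_Diff as a difference in scores, but section 2.7 introduces the ratio formula with almost the same gloss on the same variable. The parenthesis does not show that the pilot used another metric.
- *The between-group effect must be smaller than 0.6.* This does not follow. The standardiser of the 0.6 is not given; had it been the SD of scores, a between-group d on change would have a different denominator.
- *The wide pilot interval is itself an error.* It shows imprecision, as any pilot of this size would. Power is always conditional on the assumed effect, and section 2.3 does state its 0.6.

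**Conclusion.** The point holds as a gap between input and claim. The step from 0.6 to 120 is arithmetically right, but only with 0.6 as the rPMS-versus-NMS Cohen's d, and section 2.3 describes it as an effect in the rPMS group. As printed, the 90% for the superiority contrast therefore rests on a one-arm figure.

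The size depends on which quantity 0.6 is. If it is between-group, only the wording is wrong and the 90% stands, conditional on an imprecisely estimated d. If it is one-arm, the 90% is unsupported; power would be about 69% or 37% under the stated assumptions and an NMS gain of 25% or 50% of the rPMS gain. A reader might infer from these figures that the trial is underpowered. The document does not show that, since it reports no NMS result and the shares are assumed.

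**What to change.** 1. From the existing pilot data (section 2.3 already reports a result from them), compute the between-group Cohen's d as defined in section 2.8, for FMAUE_Diff as defined in section 2.7. Report it with its 95% confidence interval.
2. Reword section 2.3 to say which quantity 0.6 is.
3. State power for 120 evaluable patients as conditional on the between-group d: 90% at 0.60, 78% at 0.50, 58% at 0.40 and 37% at 0.30.
4. If 0.6 proves to be a one-arm effect, withdraw the claim that the pilot supports 90% power and keep only the conditional statement.

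The cost is a short recalculation and a few sentences. No extra patients are needed; the downside is a possibly less favourable power statement.

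### The 15% drop-out allowance was added to 120 instead of divided out, so 138 randomised leaves about 117 completers, 3 short of 120 (minor)

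*Protocol article*

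**What the plan says.** Section 2.3 sets a superiority aim ("REPMAST is designed to show the superiority of rPMS over NMS") and takes its effect size from a pilot of 20 patients, 10 per group: "we found an effect size of 0.6 on FMAUE_Diff". It asks for a size sufficient "to achieve a 90% statistical power to detect differences in FMAUE_Diff_ between the two groups", two-sided at 5%, and concludes that "a total sample size of 120 patients is required". The next sentence adds the allowance for losses: "With an estimated drop-out rate of 15%, a total sample size of 138 patients (69 in each group) is required for this study". The inflation formula is not written out.

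The Abstract repeats the total, without the 120 or the drop-out rate: "A total sample size of 138 patients (69 in each group) is required to investigate the superiority of rPMS compared with NMS". Section 2.5 gives a "1:1 allocation ratio".

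Two further parts of the article matter for the consequence. Section 2.8 plans an intention-to-treat analysis and fills missing follow-up values with the last available one. Section 2.4 schedules the Fugl–Meyer assessment four times: before treatment, at the end of weeks one and two, and at the end of week three.

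**The concern.** Section 2.3 prints three numbers that should fit together: 120 needed, 15% lost, 138 randomised. They do not. Adding 15% to the required number is a common slip. The loss applies to the larger, randomised number, so the amount added is too small to cover it.

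What is at stake is whether the stated recruitment target delivers the stated requirement at the stated loss. The base figure leaves little room: with equal groups and an exact t-test, 60 per group is the smallest size that reaches 90% power, so any shortfall below 120 takes the nominal power slightly under target.

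**Working it through.** **Inputs, all from the protocol article.** Standardised difference d = 0.6, power 90%, two-sided α = 0.05, 120 required, 15% drop-out and 138 total (section 2.3); 1:1 allocation (section 2.5); two-sample t-test for the change score if normally distributed (section 2.8).

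**Step 1: reproduce the base figure of 120.**
- Normal approximation: n per group = 2 × (1.960 + 1.282)² / 0.6² ≈ 58.4, rounded up to 59, or 118 in total.
- Exact two-sample t-test: 59.35 per group, rounded up to 60, or 120 in total. This matches the article.

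**Step 2: reproduce the total of 138.**
- 120 × (1 + 0.15) = 138. This is an exact match, and 138/2 = 69 per group.

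**Step 3: the size that keeps 120 after a 15% loss.**
- N × (1 − 0.15) = 120, so N = 120/0.85 = 141.2, rounded up to 142 (71 per group).
- Check: 142 × 0.85 = 120.7.
- Difference from the stated total: 142 − 138 = 4 patients, and 4/138 = 2.9%.

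**Step 4: what 138 delivers.**
- Completers at 15% loss: 138 × 0.85 = 117.3, about 117 (58.65 per group), which is 120 − 117 = 3 short.
- Largest loss that still leaves 120: 1 − 120/138 = 13.0%.

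**Step 5: power at d = 0.6, two-sided 5%.**

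| Completers analysed | Exact t-test |
|---|---|
| 60 + 60 = 120 | 90.3% |
| 59 + 59 = 118 | 89.8% |
| 58 + 59 = 117 | 89.6% |

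The loss is 90.3 − 89.6 = 0.7 percentage points. By the normal approximation, 58.5 per group gives 90.1%, so whether 90% is missed at all depends on the approximation used.

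**The case against.** **The number analysed need not be 117.** A reader might infer that the primary analysis will contain only 117 patients. The article does not support that. Section 2.8 plans intention to treat with values carried forward, and section 2.4 provides a baseline and two interim assessments to carry. A patient lost after any of these has a value to enter, so 117 counts completers. This objection stands, and it limits the consequence.

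It does not repair the sentence. The article adds an allowance for losses, which treats 120 as the number needed after them; if drop-outs counted in full, no allowance would be needed. Nor can full power be credited to all 138. Nominal power with 69 per group would be about 93.8%, but a patient lost before the first weekly assessment has the baseline value carried forward, so the change score is zero by the formula in section 2.7. Carried-forward values may therefore dilute the difference.

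**The shortfall is negligible for planning.** It is 3 completers and under one point of power, while the assumed effect comes from 10 patients per group. If 0.6 is a between-group d, its standard error is about √(2/10 + 0.6²/40) = 0.46, giving an approximate 95% interval of −0.3 to 1.5. This also stands. Calling the trial underpowered because of this slip would be wrong; the point is that the printed figures disagree.

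**Another route reaches 138.** The unrounded normal-approximation total, 116.8, divided by 0.85 gives 137.4, rounded up to 138. But section 2.3 starts its allowance from 120, so this does not explain the stated step.

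**The Abstract is not wrong in itself.** A reader might infer that it carries the same error. It gives 138 without the 120 or the 15%, so it contains no inconsistency and needs no change if 138 is kept.

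**Conclusion.** The point holds as a minor arithmetic error confined to the drop-out sentence of section 2.3. On the article's own figures, 138 does not retain 120 completers at 15% drop-out: about 117 remain, and 120 are retained only up to 13.0%. The correctly inflated total is 142.

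In a completers-only t-test this costs about 0.7 percentage points of power (89.6% against 90.3%). Under the planned analysis the number analysed may be higher than 117, and the article does not allow the power of that analysis to be stated.

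The conclusion rests on two readings. The 15% is taken as a share of patients randomised, which is the usual meaning; if it meant 15% of the 120, the true drop-out rate among those randomised would be 18/138 = 13.0%. The 0.6 is taken as a between-group standardised difference, which is the reading that reproduces 120.

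**What to change.** Keep 138 and restate the sentence in section 2.3, for example: *138 randomised (69 per group) retains 120 completers at up to 13% drop-out; at 15% drop-out about 117 completers remain (about 89.6% power for d = 0.6 in a completers analysis).* The closing bracket should stay, so that the power figure is not read as applying to the intention-to-treat analysis with carried-forward values.

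This costs one sentence, requires no extra enrolment and leaves the Abstract as it is. The stated power becomes marginally less favourable.

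Alternatively, the sponsor may restate the total as 142 (71 per group). That adds 4 patients, and the total must then be changed in both section 2.3 and the Abstract.
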